### Outcome measures

#### Primary outcome

The primary outcome is as follows: near final height in standard deviation score (FH SDS).

#### Secondary outcomes

Growth related:The proportion of children reaching normal adult height (− 2SD)The proportion reaching mid-parental target height (− 2SD)Difference in child’s target height minus near final height (TH-FH, in SDS and centimetres)

Bone related:Bone age delay at near final heightBone age acceleration between enrolment and near final heightBone health index at near final height

Biochemistry:Serum IGF-1 and lipid profiles (fasting lipids − serum triglyceride and total serum cholesterol) at final heightPeak stimulated GH at final height

#### Adverse events

Number of adverse events in each arm.

Health economics.Cost per percentage of children in each arm achieving target heightCost per quality-adjusted life year gained

Qualitative research:Trial acceptability (parents, patients and recruiting site staff)Reasons for declining participation in the trialParent and patient experience of the trial and treatment pathways

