#### Planned interventions

Participants in the control arm (GH +) will resume receiving their GH treatment at a dosing level determined by their clinical care team (following the minimum 6-week discontinuation period required prior to randomisation). Participants in the experimental arm (GH −) will not resume GH treatment. Both arms will be followed up at 6 monthly intervals until near FH or the 36-month follow-up (whichever is soonest).

All currently available GH treatment preparations with the active ingredient Somatropin are allowed, as detailed in the British National Formulary for Children (BNFc) in the UK and Kindermedika in Austria (https://kindermedika.at/monographie/10222/somatropin).

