#### Study procedures

Routine retesting in established puberty is routine clinical practice in all trial sites. Children with GHD persistence at retesting will restart GH; those with GHD reversal will be offered study participation. Following consent, participants will be randomised to GH + (25–35 µg/kg/day) and GH − groups and followed in routine endocrine clinics until ‘Near FH’ (growth rate < 2 cm/year) is reached. In the GH − group, any unexpected decrease in IGF-1 concentrations below − 2 SD (lower limit of normal) at 6 months would trigger a repeat GH stimulation test and recommencement of GH if deficient.

The baseline visit for all patients will include confirmation of inclusion and exclusion criteria, informed consent/assent, randomisation and allocation of trial number, prescription of growth hormone (if randomised to continue treatment), a record of the preparation and dose prescribed, a record of concomitant medication and relevant medical history. Height, weight and Tanner stage will also be measured at baseline. All patients will have 6-monthly visits to measure height, weight, Tanner stage, serum IGF-1 (at 6 months and annually thereafter) as well as checking compliance with GH therapy and any concomitant medication and adverse event reporting. HRQoL will be measured using the CHU9D questionnaire at baseline and at each 6-monthly visit. A left hand X-ray will be conducted at enrolment and near FH, for central analysis using the BoneXpert software. Fasting lipids will be measured at baseline and near FH.

At near FH, all subjects will have a GH stimulation test to reconfirm GH status. Given the usual duration of pubertal growth until near FH is achieved, we have allowed for 3 years follow-up.

The information captured at the randomisation and subsequent visits are shown in Fig. 2.

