### Secondary outcome measures

Growth and bone-related secondary outcomes will be considered non-inferiority outcomes and so will be analysed as per the primary outcome using both ITT and per-protocol analyses. Biochemistry and adverse event outcomes will be considered superiority outcomes and so will be analysed using ITT analyses only. Continuous outcomes will be analysed using linear regression models, adjusting for minimisation variables and baseline response (where applicable). Adjusted mean differences will be presented alongside 95% confidence intervals. Binary outcomes will be analysed using log binomial regression models, adjusting for minimisation variables, with both a log and identity link to obtain risk ratios and risk differences, respectively. *P*-values will only be reported for superiority outcomes. The number of participants who experience an SAE will be reported alongside the number of SAEs reported.

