### Reporting of adverse events

The collection and reporting of adverse events (AEs) will be in accordance with Regulation (EU) No. 536/2014 (Clinical Trial Safety Reporting requirements), the Medicines for Human Use Clinical Trials Regulations (2004) and its subsequent amendments, the UK Policy Framework for Health and Social Care (2017), and the requirements of the Health Research Authority (HRA).

As per routine practice AEs will be recorded in the patient’s medical notes including the documentation of the assessment of severity, seriousness and causality (relatedness) in relation to the intervention(s) in accordance with the protocol. The assessment of causality should be made with regard to the Reference Safety Information (RSI) for the GH + arm.

The reporting timeframe for adverse events will be from the date of randomisation until the participant reaches near final height or otherwise exits the study. The reporting timeframe for serious adverse events will be from the date of randomisation until the GH stimulation test is conducted at near FH. This will provide a minimum 6-week wash out period for any participants that have been receiving GH therapy.

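### Adverse events are counted per arm over a window that closes at near final height, an endpoint that treatment can move, so the comparison can be biased in either direction unless it is put on a person-time basis

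*Protocol article*

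**What the plan says.** In the protocol article, the *Adverse events* entry under *Outcome measures* is a single line: "Number of adverse events in each arm". *Secondary outcome measures* adds: "Biochemistry and adverse event outcomes will be considered superiority outcomes and so will be analysed using ITT analyses only". That section reserves P-values for superiority outcomes, so adverse event outcomes receive them. *Statistical analysis* promises between-group differences with 95% confidence intervals for every secondary outcome. The models named are linear regression for continuous outcomes and log binomial regression for binary ones. For SAEs, the number of children affected is to be given as well as the number of events. No measure is expressed per unit of time.

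*Reporting of adverse events* sets two windows, both opening at randomisation:

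- AEs: "from the date of randomisation until the participant reaches near final height or otherwise exits the study".
- SAEs: "from the date of randomisation until the GH stimulation test is conducted at near FH", with the comment "This will provide a minimum 6-week wash out period for any participants that have been receiving GH therapy".

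*Study procedures* applies the stimulation test to both arms: "At near FH, all subjects will have a GH stimulation test to reconfirm GH status".

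*Planned final analyses* defines near FH as a growth rate below 2 cm/year together with a sex-specific bone-age threshold. *Planned interventions* follows both arms every 6 months to near FH or to 36 months, whichever comes first.

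**The concern.** A raw count is a fair comparison only if both arms are observed for the same time. Here the AE window closes at an event that happens after randomisation and is defined by growth and skeletal maturation. GH acts on growth, and the trial itself plans to compare bone-age acceleration between arms. If children who stop GH fall below the growth-rate threshold sooner, they are observed for less time and contribute fewer events at the same risk. If they mature later, the distortion runs the other way. The number of children with an SAE has the same weakness, because a longer window raises the chance of at least one event.

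This bears on a conclusion the trial wants to draw. The abstract and *Discussion and potential impact* both list less exposure to adverse effects among the benefits of stopping GH. A difference in counts could be read as support for that, or as evidence against it, when it reflects only observation time.

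**Working it through.** **Inputs from the article.** Allocation is 1:1. *Sample size and power calculation* gives 57 evaluable per arm and 138 randomised, i.e. 69 per arm. Visits are 6-monthly, with a 36-month cap. The wash-out is at least 6 weeks. There is no stated AE rate, AE count, AE power or follow-up time by arm, so those below are assumptions.

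**The plan's own figure.** The only power calculation is for the primary outcome. It reproduces: 2 × (1.960 + 1.282)² × 0.9² / 0.55² = 56.3, so 57 per arm and 114 in total; 114 / 0.83 = 137.3, so 138. It does not bear on safety and serves only to fix the arm sizes used here.

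**Step 1: counts at equal rates.** With a common event rate, expected counts are proportional to mean follow-up, so the ratio of counts is T₁/T₂.

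| Mean follow-up (months, assumed) | Ratio | Fewer events in the shorter arm |
|---|---|---|
| 33 v 36 | 0.917 | 8% |
| 30 v 36 | 0.833 | 17% |
| 24 v 30 | 0.800 | 20% |

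A 3-month mean shift is what results if half the children in one arm reach near FH one visit earlier (0.5 × 6 months).

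**Step 2: effect on the test.** For a comparison of Poisson counts by normal approximation, d = (m₁ − m₀)/√(m₀ + m₁), and the two-sided type I error is Φ(−1.96 + d) + Φ(−1.96 − d). With 57 per arm and 30 v 36 months:

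- 0.5 AEs per person-year: m₀ = 57 × 0.5 × 2.5 = 71.25 and m₁ = 57 × 0.5 × 3 = 85.5, so d = 14.25/12.52 = 1.14 and the type I error is 0.21.
- 1 AE per person-year: m₀ = 142.5 and m₁ = 171, so d = 28.5/17.71 = 1.61 and the type I error is 0.36.

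With 69 per arm these become 0.24 and 0.43.

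**Step 3: participants with an SAE.** The risk of at least one event is 1 − exp(−rate × T). At 0.1 SAEs per person-year it is 0.221 at 30 months and 0.259 at 36 months, a risk ratio of 1.17 with no difference in rate.

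**Step 4: the SAE window.** Six weeks is 42/30.44 = 1.38 months. If GH− children were tested at near FH and GH+ children 6 weeks later, the extra time would be 1.38/T: 7.7% at 18 months, 5.7% at 24, 4.6% at 30 and 3.8% at 36. At 30 months with 57 per arm, expected SAEs would go from 7.1 to 7.5 (0.05 per person-year) or from 14.2 to 14.9 (0.1 per person-year), and the type I error would be 0.051–0.052.

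**Step 5: after the fix.** In the first case of Step 2, 71.25/(57 × 2.5) = 0.5 and 85.5/(57 × 3) = 0.5, so the rate ratio is 1.00.

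**The case against.** The strongest reply is that a one-line outcome label in a condensed article is not an analysis method. No model for event counts is named, a fuller SAP exists, and a log-time offset is the sort of detail a SAP holds. That is fair as far as absence goes: the lack of an offset in the article is not itself an error. What stands is that the article does fix the measure (a number of events), its status (superiority, with a P-value) and a window whose end treatment can move, and these three do not fit together.

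Second, the size is unknown. The 17–20% needs a mean shift of a whole visit interval, which nothing in the article supports. The 36-month cap limits divergence, and near FH also requires a bone-age threshold, so growth rate alone does not close the window. All of this stands. The cap helps only children who reach it, however, and *Missing data and sensitivity analyses* expects failure to reach near FH to be rare.

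Third, a reader might infer that the SAE window is at least 6 weeks longer for children on GH. The article does not say so. Both arms share one endpoint, the stimulation test at near FH, and the 6 weeks is a minimum wash-out for those who received GH, not a stated difference between arms. A gap arises only if GH− children are tested sooner, and that timing is not given. GH− children who had recommenced GH would have the wash-out too. Collecting SAEs through the wash-out also has a plain safety purpose and should not be criticised.

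**Conclusion.** The point holds as a mismatch between measure and window. A raw count is to be compared over follow-up that ends at a treatment-sensitive endpoint, so the AE comparison can be biased. It would go too far to say that it is biased, because the documents give neither the direction nor the size of any difference in time to near FH. Under assumed mean shifts of 3 to 6 months the spurious deficit is about 8% to 20%. The inflated type I errors in the working rest on the 6-month shift and on assumed event rates.

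The SAE wash-out is secondary: about 4–8% of follow-up over 18–36 months, conditional on unstated test timing, with almost no effect on type I error at the SAE rates tried.

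The window's end also needs one consistent definition. *Planned interventions* stops follow-up at 36 months at the latest, while the Fig. 2 legend allows longer. The bone-age thresholds are assigned to the sexes in opposite ways in that legend and in *Planned final analyses*, and *Study procedures* gives growth rate alone. These passages must be reconciled.

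**What to change.** - Report person-time at risk by arm, for AEs and for SAEs.
- Make the between-arm comparison a rate ratio per person-year with its 95% confidence interval, from a negative binomial or robust Poisson model with log follow-up time as offset. Keep the event counts and the number of children with an SAE as description.
- For SAEs, either let the same offset run to each child's stimulation test, or end the between-arm comparison at the near-FH or 36-month visit in both arms. In the second case, continue to collect later SAEs and list them separately.
- Use one definition of near FH and of the end of follow-up throughout.

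The cost is wording in the protocol and SAP, one extra model and a person-time table. Randomisation, visit and event dates should suffice, so no new assessment is needed, and *Trial status* says no patient had been recruited at publication. One limit remains: the offset removes the distortion fully only if event rates are roughly constant over follow-up.

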#### Data management

All processes are detailed in the study protocol and in the GHD Reversal Trial data management plan.

### Statistical analysis

A separate statistical analysis plan (SAP) has been produced which provides a more comprehensive description of the planned statistical analyses which is available from the corresponding author on request. The primary comparison groups will be composed of those treated with GH (25–35 μg/kg/day) versus those not treated with GH. Non-inferiority outcomes will be analysed using both intention-to-treat (ITT) (i.e. all participants will be analysed in the treatment group to which they were randomised, irrespective of compliance or other protocol deviation) and per-protocol analyses (i.e. those participants who are considered adherent to their allocated intervention, as defined in the SAP). This is because an ITT analysis alone may bias results in favour of non-inferiority. Superiority outcomes will be analysed using ITT analyses only. For all primary and secondary outcome measures, summary statistics and differences between groups will be presented with 95% confidence intervals. Outcomes will be adjusted for the minimisation variables and baseline values where appropriate. No adjustment for multiple comparisons will be made.

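### Adverse events are restricted to ITT analysis; a supportive table by GH actually received should stand beside it

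*Protocol article*

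**What the plan says.** The protocol article's Statistical analysis section gives non-inferiority outcomes both an ITT and a per-protocol analysis, with the reason: "This is because an ITT analysis alone may bias results in favour of non-inferiority". For the rest, "Superiority outcomes will be analysed using ITT analyses only". ITT is defined so that "all participants will be analysed in the treatment group to which they were randomised, irrespective of compliance or other protocol deviation".

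The Secondary outcome measures section applies this to harms explicitly: "Biochemistry and adverse event outcomes will be considered superiority outcomes and so will be analysed using ITT analyses only". The outcome itself is given as "Number of adverse events in each arm" (Adverse events), with AEs collected "from the date of randomisation until the participant reaches near final height or otherwise exits the study" (Reporting of adverse events).

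Under Study procedures, a GH− child whose IGF-1 falls below −2 SD at 6 months has a route back to treatment: the fall "would trigger a repeat GH stimulation test and recommencement of GH if deficient". The same section lists the content of the 6-monthly visits, "as well as checking compliance with GH therapy and any concomitant medication and adverse event reporting". The article gives no expected restart rate, non-adherence rate or adverse event rate, and mentions no safety analysis by treatment received.

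**The concern.** Under this rule, a reaction to GH in a GH− child who has restarted is tabulated under GH−, and any GH-free time in a GH+ child counts as GH+ follow-up. Both move the arms together for events that GH causes. The plan recognises this mechanism for height and adds a second analysis population there, but allows none for harms.

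It matters because reduced exposure to GH adverse effects is among the stated benefits of the new pathway (Abstract, Discussion; Discussion and potential impact), and the latter section says that some controversy over GH safety remains. That question is about exposure to GH. A count by allocation alone answers it only indirectly. P-values are reserved for superiority outcomes, so any formal test for adverse events would also rest on the diluted contrast.

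**Working it through.** **The plan's own figure.** The only calculated quantity is the sample size, and it reproduces. With margin 0.55, SD 0.9, one-sided alpha 0.025 and 90% power, n per arm = 2 × (1.960 + 1.282)² × 0.9² / 0.55² ≈ 56.3, so 57, or 114 in total. Then 114 / (1 − 0.17) = 137.3, so 138, or 69 per arm. It is not in dispute, and it says nothing about power for harms.

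**Dilution formula.** Let *a* be the event rate on GH and *b* the rate off GH, for events that GH can cause. Let *r* be the share of GH− follow-up spent on GH and *s* the share of GH+ follow-up spent off GH.

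- Rate in GH+ = a(1 − s) + b·s
- Rate in GH− = b(1 − r) + a·r
- ITT difference = (a − b)(1 − r − s)

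The direction follows from the design: any r or s above zero shrinks the difference. The size does not, because *a*, *b*, *r* and *s* are all absent from the documents.

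**Illustration with assumed rates** of 0.30 per year on GH and 0.15 off GH (true ratio 2.00, difference 0.15):

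| r | s | GH+ rate | GH− rate | Difference | Share of difference lost | ITT rate ratio |
|---|---|---|---|---|---|---|
| 0 | 0 | 0.3000 | 0.1500 | 0.1500 | 0% | 2.00 |
| 5% | 5% | 0.2925 | 0.1575 | 0.1350 | 10% | 1.86 |
| 5% | 10% | 0.2850 | 0.1575 | 0.1275 | 15% | 1.81 |
| 10% | 20% | 0.2700 | 0.1650 | 0.1050 | 30% | 1.64 |
| 10% | 30% | 0.2550 | 0.1650 | 0.0900 | 40% | 1.55 |

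**Effect on power, again with assumed risks.** The same factor is applied to the risk of at least one GH-caused event, with 69 children per arm and a two-sided 5% test:

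- 10% off GH v 30% on GH: power is 84% with no crossover, 76% at r = s = 5%, 66% at 10%/10% and 42% at 20%/20%.
- 5% v 15%: power is 50% with no crossover, 35% at 10%/10% and 22% at 20%/20%.

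The second line shows that, for less common events, power is limited even before any crossover.

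**What the text implies about r and s.** Entry requires a normal GH re-test and a normal IGF-1 (Inclusion criteria). Restart needs a low IGF-1 followed by a deficient repeat test (Study procedures). Both suggest that r is small. Known persistent non-compliance is an exclusion (Exclusion criteria), which should limit s, though daily injections over up to 36 months leave room for it. The upper rows of the table are therefore easier to reconcile with the text than the lower ones, but nothing in the article settles this.

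**The case against.** The strongest reply is that restart is part of the GH− strategy. The trial compares stopping, with restart if deficient, against continuing. An event after a protocol-specified restart is a real consequence of that policy, and ITT counts it where it belongs. This stands, and it is why ITT should remain the main analysis.

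Second, the parallel with height is incomplete. For height, dilution favours the conclusion that the trial hopes for. For harms, the hoped-for result is fewer events after stopping, and dilution makes that harder to show. A reader might infer that the ITT rule tilts the safety comparison in favour of the new pathway; the documents do not support that. What is lost is sensitivity.

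Third, the Reporting of adverse events section requires severity, seriousness and causality to be assessed for every event, so a GH reaction in a restarted child can be recorded as related to GH. This stands in part. Causality coding labels individual events but supplies no exposure-based denominator, and the reference safety information is tied to the GH+ arm, which leaves its use for restarted GH− children unclear.

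Fourth, 'only' may be aimed at the per-protocol analysis rather than at descriptive safety tables, which the separate SAP may contain. That is possible. But the restriction is stated twice and names adverse events, so a SAP that adds an exposure-based analysis would sit uneasily with it.

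Finally, an on/off-GH comparison has limits of its own. It is not randomised; every child had GH before the trial, so time off GH is not unexposed time; and the Discussion describes some of the harms as rare, while others (bone tumours, cerebrovascular events) are reported in patients treated earlier. A trial of 138 children is unlikely to resolve such harms under either analysis. All of this stands, and limits the extra table to a supporting role.

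**Conclusion.** The point holds as an inexpensive improvement to the safety analysis. The protocol fixes an ITT-only rule for adverse events while providing a route back to GH in one arm and checking compliance in the other. For GH-caused events this dilutes the difference by (1 − r − s): by 10% to 40% across the assumed shares tabulated above, and by nothing if there is no crossover. The effect may well be small. Events unrelated to GH are not affected in this way.

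A reader might go further and infer that the plan conceals harm, or that ITT is the wrong analysis here. Neither follows. ITT is valid for the comparison of strategies, the extent of crossover is unknown, and no stated figure or primary conclusion changes. The supported conclusion is narrower: a count by allocation alone is a less sensitive and partly misattributed summary of harm from GH exposure. The clinical restart rule is not in question.

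**What to change.** - Keep the ITT table of AEs and SAEs as the main safety comparison.
- Remove 'only' as it applies to adverse events, in both Statistical analysis and Secondary outcome measures.
- Pre-specify one supportive table of AEs and SAEs by GH actually received: each event classed as on or off GH at onset, with rates per person-year. AEs and SAEs have different end points for reporting, so each needs a denominator that matches its own window.
- Confirm that the 6-monthly compliance record captures GH start and stop dates. The article mentions compliance checks but not dates, and on/off person-time cannot be built without them.
- Pre-specify an attribution window after GH stops. The minimum 6-week wash-out in Reporting of adverse events is one candidate; there it explains the end of SAE reporting and is not an existing attribution rule.
- Label the table as non-randomised and supportive, and note that all children were exposed to GH before randomisation.

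The cost is a small wording change and one extra table, plus a data field if start and stop dates are not already collected. Design, sample size and primary analysis are untouched. The Trial status section reports no patients recruited at publication, so at that point the table could be fixed before any data existed.
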